## Abstract

**Background:**

Cardiovascular disease remains the leading cause of morbidity and mortality worldwide, and there is a rising global burden. The effects of diet on cardiometabolic risk factors have been studied extensively. Healthy eating as a cost-effective approach to risk reduction in post-myocardial infarction patients is proven to be beneficial, and the “plate model” is one of the practical methods to achieve this objective.

**Methods/design:**

The study will be conducted as a randomized, single-blind, controlled clinical trial for a period of 3 months. A total of 120 overweight (body mass index >23 kg/m^2^) inpatients (aged 20–70 years) with a history of troponin-positive acute coronary syndrome (ACS) within the 1 month preceding the study will be recruited. Simple randomization will be used in participant allocation. The intervention group will receive the model plate diet. The control group will be provided with routine dietary advice. Other domains, such as advice on exercise and lifestyle modification, will be equalized among patients in both the groups. The visits and evaluations will be done at recruitment (visit 0), 4 weeks, and 12 weeks after the intervention. The primary outcome will be a mean body weight reduction of 10%, and the secondary outcomes will include mean reduction of systolic and diastolic blood pressure, improvement of anthropometric parameters, and improvement of lipid profile and liver enzymes in the test group compared with the control group at 12 weeks following the plate model diet.

**Discussion:**

This study protocol is designed to establish the effects of the plate model diet on modification of cardiometabolic risk factors in patients with ACS. This will also be a pioneering study designed to investigate the practicality of the model plate in local settings and in the South Asian region.

**Trial registration:**

Sri Lanka Clinical Trials Registry identifier: SLCTR/2016/22. Registered on 22 September 2016 (http://www.slctr.lk/trials/483).

**Electronic supplementary material:**

The online version of this article (doi:10.1186/s13063-017-2057-6) contains supplementary material, which is available to authorized users.

## Background

The World Health Organization (WHO) estimates that cardiovascular disease (CVD) is the leading cause of death globally [1]. Current data on the global impact of CVD show that the highest mortality due to CVD will occur predominantly in developing countries in the next decade [2]. An estimated 17.5 million people died as a result of CVD in 2012, representing 31% of all global deaths. Of these deaths, an estimated 7.6 million were due to coronary heart disease. More than three-fourths of CVD-related deaths occur in low- and middle-income countries [3]. According to another systematic review, the global burden of ischemic heart disease (IHD) increased by 29 million disability-adjusted life-years (a 29% increase) between 1990 and 2010 [4].

There are two approaches to the prevention of CVD, and they are population-wide and individual [1]. The expected goals of CVD morbidity and mortality reduction can be accomplished only through a combination of both approaches. Although large-scale studies have shown effective strategies to prevent CVD-related deaths in the past decade, most of the evidence was accumulated from the developed regions of the world. Hence, there is a need to conduct studies in different geographic regions, diverse cultures, and various ethnicities to address the paucity of high-quality data in developing countries. The INTERHEART study is a good example of a study with broader geographic and ethnic representation. INTERHEART, representing every inhabited continent, has provided a multitude of relevant data on a global scale [5]. The INTERHEART researchers have studied the association of a selection of nine risk factors for myocardial infarction (MI) and their population attributable risk. Their study showed that abnormal lipid levels, smoking, hypertension, diabetes, abdominal obesity, psychosocial factors, alcohol use, reduced consumption of fruits and vegetables, and lack of regular physical activity account for most of the risk of MI worldwide in both sexes and in all age groups in all regions [6].

As a “best buyer,” the WHO recommends healthy eating to be one of the most cost-effective preventive strategies on an individual basis [1]. Reduction of salt and fat in the diet and consumption of fruits and vegetables have long been known to yield protective effects on the heart for both primary and secondary prevention of CVD. The investigators in the Lyon heart study examined 605 patients aged 55–80 years with previous MI and found that the benefits of the Mediterranean diet could be extended to the secondary prevention of CVD. Those who followed the Mediterranean diet had a 50% to 70% lower risk of recurrent heart disease compared with those who followed a diet similar to the American Heart Association (AHA) Step-1 diet [7]. The combination of diet and statin treatment in preventing cardiovascular events was studied by Pitsavos et al. [8], and they observed a synergistic effect of a combination of the Mediterranean diet with statin treatment on coronary risk. In particular, they observed that the aforementioned combination was associated with a 43% reduction in coronary risk, independent of cholesterol levels and other cardiovascular factors [8]. According to a hospital-based case-control study conducted in India, a significant dose-dependent inverse association between vegetable intake and IHD risk exists. The inverse association was stronger for green leafy vegetables, and persons consuming a median of 3.5 servings of green leafy vegetables per week had a 67% lower relative risk than did those consuming 0.5 serving per week [9].

Dietary patterns in Sri Lanka are changing at a faster pace than ever because of rapidly evolving urbanization. Consequently, the last 2 decades have seen a threefold increase in the level of obesity among Sri Lankan adults [10]. In 2010, it was reported that the prevalence rates of overweight, obese, and centrally obese people in Sri Lanka were 25.2%, 9.2%, and 26.2%, respectively [11]. Obesity-associated metabolic diseases also have reached epidemic proportions in Sri Lanka. The prevalence of metabolic syndrome is 25% [12], hypertension approximately 20% [13], and dysglycemia 21% [14]. These comorbid factors invariably increase health care expenditures of obese persons [15]. In 2014, noncommunicable diseases accounted for 75% of the total deaths in Sri Lanka, of which CVD-related deaths alone accounted for 40% [16]. According to a study conducted in Sri Lanka, a substantial proportion of the adult population fails to follow recommended dietary guidelines [17]. Almost 70% of those studied exceeded the recommendations for starch intake; in contrast, the daily intake of fruit (0.43 servings/day) and vegetable portions (1.73 servings/day) fell well below national recommendations, with only 3.5% of adults consuming the recommended five portions of fruits and vegetables per day [17]. Thus, Sri Lankans consume over 70% of their calories as carbohydrates (mainly refined), whereas only 10% of calories are derived from protein [18]. This is not surprising, because rice is the main staple food in Sri Lanka [19]. Hence, cutting down the amount of rice per meal might be a solution to the problem of excessive intake of refined carbohydrates and energy.

Using a “model plate” is one of the practical methods to reduce the average portion size of staple food in main meals, which also could ensure the sufficient intake of vegetables and protein foods simultaneously. Food and nutrition experts recommend the “plate model” to control the rice portion and to replace it with nonstarch vegetables [20]. The local [21] and international [22] expert evidence supports the plate model for the promotion of healthy eating, whose aim is at dietary calorie reduction and redistribution of macronutrients in a healthier manner. By devising the plate model, one can ensure an increased intake of complex carbohydrates from dark green leafy salads and nonstarchy vegetables as well as high fiber from whole grain, thus lowering the glycemic load in food. Dietary fiber intake reduces chronic inflammation [23], which is one of the postulated pathophysiologies of atherosclerosis [24]. Increased consumption of vegetables ensures the high intake of beta-carotene, vitamins C and E, polyphenols, and minerals, which are vital in sustaining bodily functions. Furthermore, increased intake of plant sterols and stanols decreases the absorption of cholesterol and thereby reduces serum cholesterol levels [25], particularly low-density lipoprotein (LDL) cholesterol [26].

Although evidence exists to guide the diet of patients in post-MI rehabilitation, the lack of standard guidelines in Sri Lanka has led clinicians to commence their patients on various untested dietary schedules. Therefore, scientific evaluation of the effects of a balanced diet with the use of a plate model and its impact on coronary risk factor modification needs to be assessed locally as well as globally. In the present study protocol, we are trying to depict the method of one such study to evaluate the effects of a plate model diet on modification of selected cardiometabolic risk factors in post-MI patients.

## Methods/design

### Objectives and hypothesis

The aim of the present study is to evaluate the effects of a plate model on modification of selected cardiometabolic risk factors in patients with a history of MI. Our hypothesis is that intake of a healthy diet using the model plate will improve coronary risk factors with an expected mean weight reduction by 10% in the test group after adopting the plate model diet for a period of 12 weeks and reduction of total cholesterol, LDL cholesterol, total cholesterol/high-density lipoprotein (HDL) ratio, blood pressure (BP), and alanine aminotransferase (ALT) compared with the control group.

### Study design

This proposed study is an interventional, randomized, single-blind study with parallel subject allocation of patients with a history of troponin-positive acute coronary syndrome (ACS). A summary of the study protocol is presented in Fig. 1. The Standard Protocol Items: Recommendations for Interventional Trials (SPIRIT) checklist is presented in Fig. 2 and Additional file 1.

**Fig. 1 Fig1:**
[figure not shown]
Schematic representation of the study protocol. *ALT* Alanine aminotransferase, *FBS* Fasting blood sugar

**Fig. 2 Fig2:**
[figure not shown]
The schedule of enrollment, interventions, and assessments

### Sample size

The sample size will be selected on the basis of a pilot survey, and the number needed for recruitment will be determined to account for a confidence level of 95%, a confidence interval of 10%, and 80% statistical power. A 10% hypothesized difference of participants’ body weight between the control and intervention groups following the plate model diet at the end of 12 weeks is taken as the primary outcome when calculating the sample size. Because the other biochemical parameters (BP, lipid profile, fasting blood sugar [FBS], and ALT) are prone to vary with medication and compliance with medication, they were not regarded in sample size calculations. A subsequent 5% withdrawal rate and another 15% loss to follow-up (total of 20%) are accounted for in the calculation. A total sample of 120 will be recruited over an anticipated period of 3 months.

### Study setting

The study is being conducted at the Institute of Cardiology, National Hospital of Sri Lanka, which is a tertiary care facility for patients with cardiac disease.

### Study population

The subjects will be voluntary participants admitted to the cardiology unit at the National Hospital of Sri Lanka and diagnosed with troponin-positive ACS. Subjects who fulfill the inclusion and not the exclusion criteria will be selected for the study. Patients with troponin-positive MI (i.e., ST-elevation MI or non-ST-elevation MI) or patients who fulfill the electrocardiogram (ECG) criteria as defined by the World Heart Federation Task Force for the Universal Definition of Myocardial Infarction [27] will be recruited to take part in the study, regardless of the troponin quantitative assay. Furthermore, new or presumably new left bundle branch block and true posterior MI have been considered as an ST-elevation myocardial infarction (STEMI) equivalent. Study participants will be recruited into the study after their written informed consent is obtained.

### Inclusion criteria

Post-MI patients admitted to the tertiary care facility who fulfill all of the following criteria will be selected for the study:Aged between 20 to 70 yearsPatients with a troponin-positive ACS during the 1 month preceding the date of recruitment, regardless of history of unstable angina

o STEMI defined as new ST elevation at the J-point in at least two contiguous leads of ≥2 mm (0.2 mV) in men or ≥1.5 mm (0.15 mV) in women in leads V2–V3 and/or of ≥1 mm (0.1 mV) in other contiguous chest leads or the limb leads, as well as new or presumably new left bundle branch block
o Non-ST-elevation MI is diagnosed in the absence of the aforementioned ECG changes, although in the presence of cardiac biomarker positivity (according to American College of Cardiology/AHA guidelines) cutoffs for troponin I >0.5 ng/ml and creatine kinase 5.0 ng/ml are used. The diagnosis is made by the admitting medical officer, and before recruiting the patient, the investigator will also confirm the presence of the above-described criteria.
Patients who have had the index coronary event that led to the current hospital admission within the preceding 1-month periodPatients who consume rice as a staple food for at least two main meals per dayPatients who consent and are able to attend clinic follow-up visits on a monthly basisPatients who are eating homemade food for at least two main meals per dayPatients whose body mass index (BMI) is greater than 23 kg/m^2^

### Exclusion criteria

Patients who fulfill the following criteria will be excluded from the study:Patients who are in end-stage renal failure (stage III or higher), have congestive cardiac failure (New York Heart Association class III and above), have chronic liver cell disease (Child-Pugh class B or above), have severe anemia (hemoglobin <8.0 g/dl for both men and women), or have other severe systemic disease at the time of recruitmentPatients who are pregnant or breastfeeding.Patients who have had any documented infection with systemic effects (i.e., high-grade fever, abnormal leukocyte count >11,000/μl, or erythrocyte sedimentation rate >22 mm/first hour for men and 29 mm/first hour for women) within the last 2 weeksPatients who are already on a modified diet or taking dietary supplements

### Suspension criteria

Patients may be withdrawn from the study in the following circumstances:Subject demands to discontinue the studyUnusual changes in clinical test resultsPrincipal investigator’s decision to terminate the study (low rates of compliance, complications, or inability to sustain the study for various reasons)

### Randomization

The first subject will be randomized to the control or intervention group by tossing a coin. Subsequently, the study subjects will be allocated alternatively to either group until such point that the expected sample number is reached. The subjects will be stratified according to sex, and an even quota of male and female subjects in both groups will be ensured. The allocation sequence will be closely monitored by two of the study authors (PF and RJ). Only the patients who satisfy the aforementioned inclusion and exclusion criteria will be selected for the study.

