As part of this 12-week hospital- and home-based intervention, each participant in the intervention group will be provided with a model plate along with the food poster and a food diary. The patients will also be provided with nutrition advice that will be customized according to patients’ social, economic, and personal preferences by a trained research assistant (PF) with close supervision of a nutrition specialist (RJ). Advice in other domains, such as physical activity and lifestyle modification (e.g., cessation of smoking, cutting down alcohol and intake of drugs), will be evenly provided to both the groups as part of routine care by the discharging nursing officer.

Two specially designed booklets will be provided to the patients to standardize the health education delivered to the patients verbally. The first booklet will contain information regarding the step-up plan of exercise following MI in both hospital and home settings. The second booklet gives information regarding lifestyle modifications following MI, such as cessation of smoking, regular sleeping, and resuming sexual activities. Both the booklets will be provided to the control and intervention groups. Furthermore, to enhance knowledge on different food choices under each category/color, a food poster will be given to the patients who will be following the plate model diet.

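### Allocation is a coin toss followed by alternation: predictable quasi-randomisation, not the simple randomization that the abstract claims

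*Protocol article*

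**What the plan says.** The Randomization section gives the rule in two sentences: "The first subject will be randomized to the control or intervention group by tossing a coin", and then "Subsequently, the study subjects will be allocated alternatively to either group until such point that the expected sample number is reached". It adds: "The subjects will be stratified according to sex, and an even quota of male and female subjects in both groups will be ensured". It also says that two study authors, identified by initials, watch the sequence closely.

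The Methods/design paragraph of the abstract describes something else: "Simple randomization will be used in participant allocation". That paragraph and the Study design section both use the word randomized; Study design has "interventional, randomized, single-blind study with parallel subject allocation".

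Three other places bear on who could act on the sequence:

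- **Day 2 until discharge:** the initials of the two sequence monitors reappear. One of the two gives the individual nutrition advice and the other, a nutrition specialist, supervises it.
- **Inclusion criteria:** "before recruiting the patient, the investigator will also confirm the presence of the above-described criteria". The Day 1 section has an investigator explain the study before consent.
- **Blinding:** the cardiologist, medical officers and nurses are not told the assigned arm.

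**The concern.** Alternation is not random allocation. After the starting toss, the next arm follows from the last one. A person who knows the last allocation and has any say in who is approached, when consent is taken, or which of two eligible patients is entered first can influence which arm a patient joins.

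Some entry criteria leave room for judgement, such as ability to attend follow-up and the absence of other severe systemic disease. In a diet trial, willingness to change eating habits is plausibly related to weight loss, and it is not among the data listed for Day 1. Covariate adjustment could not be relied on to correct an imbalance in it.

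The Discussion defends body weight as an objective outcome. That protects against biased measurement but not against arms that differ at entry. The p-values would also lose the basis that random assignment gives them, and a reader of the abstract would not know it.

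**Working it through.** **1. How much of the list is random.** Input: N = 120 (Sample size section).

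| Scheme | Possible sequences | Assignments fixed in advance |
|---|---|---|
| One toss, then alternation | 2 | 119 of 120 |
| One toss per sex, alternation within sex (an assumed reading) | at most 4 | at least 118 of 120 |
| Simple randomization | 2^120 | 0 |

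**2. How predictable the next arm is.** Expected correct guesses over 120 assignments, made by someone who knows all past assignments:

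- One alternating sequence: 0.5 + 119 = 119.5, or 99.6%.
- Alternation within two sex strata: 2 × 0.5 + 118 = 119, or 99.2%.
- Permuted blocks of random size 4 or 6, one stratum (simulated): about 83, or 69%.
- Simple randomization: 120 × 0.5 = 60, or 50%.

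This step uses only the stated rule and N.

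**3. What exploiting it could do (illustration).** Assumptions, none of them from the documents: in a fraction f of adjacent pairs, the patient judged more likely to lose weight is placed in the plate arm; that judgement has correlation r with the outcome; there is no true effect. The expected gap between the larger and smaller of two standard normal values is 2/√π = 1.128, so

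bias (in SD) = 1.128 × r × f.

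- Low end: 1.128 × 0.3 × 0.2 = 0.07.
- High end: 1.128 × 0.5 × 0.5 = 0.28.

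Simulated rejection rates of a two-sided 5% t test, 60 per arm:

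| Pairs steered | r = 0.3 | r = 0.5 |
|---|---|---|
| 20% | 6.5% | 9.4% |
| 30% | 8.6% | 15.4% |
| 50% | 15.3% | 33.9% |

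With no steering, the simulated rate was 4.9%.

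**Hand check,** with SE = √(2/n) and rate = Φ(−1.96 + bias/SE) + Φ(−1.96 − bias/SE):

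- n = 60, SE = 0.183. Low: 0.0677/0.183 = 0.37, giving 6.6%. High: 0.282/0.183 = 1.54, giving 34%.
- n = 48 (the planned 20% loss: 120 × 0.8 = 96, or 48 per arm), SE = 0.204. Low: 0.0677/0.204 = 0.33, giving 6.3%. High: 0.282/0.204 = 1.38, giving 28%.

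The 48-per-arm figures are the closer match to the plan, because Monitoring and data management removes dropouts from the database.

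**The case against.** The alternation rule itself has no good defence. It is a stated method, not a detail left to a fuller document, and nothing else in the article restores randomness. The objections concern what may be inferred from it.

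- **The sex quota.** A reader might infer that alternation cannot deliver the promised balance and that staff must override the sequence by hand. That requires a single sequence running across both sexes. The text says patients are stratified by sex, and alternation within each sex would balance the arms to within one patient per sex. The article does not spell out how the two sentences combine, but it does not support a charge of manual override.
- **Concealment.** A reader might infer that concealment is impossible and that every assignment can be predicted with certainty. Predictability requires knowledge of the previous allocation. The two authors are said to monitor the sequence, not to enrol; enrolment tasks fall to an unspecified investigator, and concealment details could sit in a fuller protocol. This stands. What remains is that the rule makes the next arm deducible from the last, and that the article describes nothing to keep that knowledge from the people enrolling.
- **The 50% comparator.** It flatters the alternative. If past assignments are known, the blocked scheme recommended here is itself guessed about 69% of the time. This stands, and it is why the block sizes should vary and the list be held outside the recruiting team.
- **The bias figures.** The steering rates and correlations are assumed, begin at 20%, and require two eligible patients to be available together. They illustrate; they do not estimate.

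Blinding the ward team does not answer the point. It conceals the arm from clinicians after assignment, whereas the risk arises before it.

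**Conclusion.** The point holds. The article describes quasi-randomised allocation with at least 118 of 120 assignments fixed in advance, and this contradicts its own claim of simple randomization and its randomized label. That conclusion rests on the text alone.

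Selection bias at enrolment is therefore possible, and the dual role of the two sequence monitors makes it a more serious risk. The documents do not show that anyone has steered enrolment, and that should not be inferred. The illustrative consequence is a bias of 0.07–0.28 SD, with a true error rate of about 6.5–34% at 60 per arm or about 6–28% at 48 per arm. It depends wholly on the assumed f and r and falls to zero if nobody steers. The allocation rule should be changed whatever values are thought likely.

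**What to change.** Amend the Randomization section so that all remaining patients are allocated as follows: 'Allocation follows a computer-generated list, stratified by sex, in permuted blocks of randomly varying size. The list is prepared and held by a person not involved in recruitment or dietary counselling. Each assignment is released only after consent and the Day 1 baseline measurements are complete.' Change the abstract's description of the method to match.

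The Trial status section says recruitment is under way, so three further steps are needed:

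1. Record the date of the switch and the number of patients allocated before it.
2. Describe patients allocated by alternation as quasi-randomised wherever the trial is called randomized.
3. Report a sensitivity analysis restricted to patients allocated after the switch.

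The cost is a protocol amendment, one generated list and an independent holder for it; no visits are added. The main limitation is that Study period plans only 12 weeks of recruitment, so few patients may remain and the sensitivity analysis may be too small to be informative. If so, the report should say so and rely on the quasi-randomised label.
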